### 2.6 Study Outcomes

Treatment outcomes are defined in accordance with the Ahmed et al. (31, 32) proposal for standardization of terms and reporting criteria for imaging-guided ablation.

#### 2.6.1 Primary Outcomes

The primary outcomes are the complete ablation rate at 1 month, and adverse events. The later may be device-related, intraprocedural, postprocedural, or late, and will be reported using the NCI Common Terminology Criteria for Adverse Events (CTCAE) (**Supplementary Appendix 2**).

#### 2.6.2 Secondary Outcomes

The secondary outcomes are the following: technical success, technique efficacy, characteristics of the nsPEF procedure, local tumor progression (LTP), and local progression-free survival (LPFS). Specifically, technical success addresses whether the tumor is treated according to protocol and covered completely by the ablation zone; tumor coverage will be assessed immediately after the nsPEF procedure by CEUS.

Technique efficacy is regarded as radiologic complete ablation achieved after as many as 2 iterative nsPEF procedures. The nsPEF procedure characteristics include the following: number of electrodes used; active tip length of the electrodes; distance between electrodes; rate of pullback applications; total number of pulses delivered per procedure; total procedural time; ablation time; ablation volume; and sufficient ablative margin.

LTP describes the reappearance of HCC adjacent to the ablated zone after successful treatment. LPFS is defined as the time from the commencement date of the nsPEF procedure to the date of local progression. LPFS will be censored at the date of the last follow-up, when the patient has no evidence of local progression.

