### 2.2 Patient Population

Potential trial participants will be identified at an institutional multidisciplinary tumor board, comprised of interventional radiologists, hepatobiliary surgeons, medical oncologist, and diagnostic radiologists. The potential subjects will subsequently be referred for enrollment and eligibility screening. All candidates will be reviewed for safety and eligibility by an experienced interventional radiologist, participating in the research project at each center. All eligible patients will be explained about the study protocol in details. Only those who sign the consent form will enter the trial. The inclusion and exclusion criteria are listed in **Table 2**.

**Table 2 T2:** Patients inclusion and exclusion criteria.

Inclusion criteria	Exclusion criteria
HCC diagnosed histologically or clinically according to the guidelines of the American Association for the Study of Liver Diseases tumors located immediately (<0.5 cm) adjacent to the portal vein, hepatic veins, bile duct, gastrointestinal tract, or diaphragm age ≥ 18 years no evidence of extrahepatic metastasis single tumor with a maximum diameter of ≤5cm, or the number of tumors of ≤3 and a maximum diameter of ≤3cm. Child-Pugh A or B Performance status according to Eastern Cooperative Oncology Group (ECOG) ≤2. written informed consent	Ventricular cardiac arrhythmia Congestive heart failure, NYHA Class ≥ 3 Active coronary artery disease History of epilepsy Any implanted stimulation device Other treatment <6 weeks prior to treatment presence of vascular invasion or extrahepatic metastasis. Severe coagulation abnormalities

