### 2.5 Postprocedural Follow-Up

After the procedure, all patients will be monitored for at least another day in inpatient department, in accordance with current medical practice. Routine laboratory studies, electrocardiogram, and CEUS will be performed to assess procedure-related complications.

Contrast-enhanced MRI will be performed 1 month after the procedures to evaluate technique efficacy. Complete ablation is considered complete nonenhancement of the treated tumor, and incomplete ablation is the presence of residual tumor on contrast-enhanced MRI. In the event of incomplete ablation, an additional nsPEF procedure will be conducted with the same technique. If the residual tumor is still viable after the second session, then nsPEF is considered failed, and the patient will be excluded from the trial and referred to other therapies.

If efficacy is confirmed, then clinical, biological, and radiological examinations are required every 3 months during the first year, and once every 6 months thereafter. Baseline and follow-up images will be interpreted independently by all experienced diagnostic abdominal radiologists. At the end of the trial, 2 independent radiologists will review all images before and after treatment, and reach a consensus.

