### 2.7 Calculation of Sample Size

Because this is a pilot study, there is currently no data on the complete ablation rate of nsPEF for the treatment of HCC. Previous studies showed a 77.3%-86% rate of complete ablation after the first IRE (with a traditional microsecond duration) in patients with HCC that was not appropriate for thermal ablation (11, 33). Our hypothesis is that 80% of tumors treated by nsPEF will achieve complete ablation by the 1-month follow-up. For the single arm OPC hypothesis, employing 80% power and with a 2.5% one-sided α, then 160 patients will be required. Assuming a 20% rate of withdrawal or loss during follow-up, 192 participants should be enrolled.

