### 2.8 Statistical Methods

Continuous data will be expressed as median and range. Categorical variables will be shown as frequency and proportion. Survival curves and cumulative incidence of LTP will be generated using the Kaplan-Meier method. The Cox proportional hazards method will be used for univariate and multivariate analyses to determine prognostic factors. Technical success, technique efficacy, nsPEF procedural characteristics, and local tumor progression will be analyzed per tumor. The rate of adverse events and local progression-free survival will be analyzed per patient. *P* values < 0.05 will be considered statistically significant. All statistical analyses will be performed with a software package (SPSS, version 23.0; SPSS, Chicago, Ill).

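### Local progression-free survival is named as survival but defined without death, so if patients die without local progression the reported curve lies above true survival free of local progression

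*Protocol article*

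**What the plan says.** Section 2.6.2 of the protocol article fixes the start, the event and the censoring rule of this secondary outcome. On start and event: "LPFS is defined as the time from the commencement date of the nsPEF procedure to the date of local progression". On censoring: "LPFS will be censored at the date of the last follow-up, when the patient has no evidence of local progression". Neither sentence mentions death, and no other section shown gives a rule for it.

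The same section defines the related outcome, local tumor progression (LTP): "LTP describes the reappearance of HCC adjacent to the ablated zone after successful treatment".

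Section 2.8 names one estimator for both: "Survival curves and cumulative incidence of LTP will be generated using the Kaplan-Meier method". It names no method for competing events. It also sets the unit of analysis: "The rate of adverse events and local progression-free survival will be analyzed per patient". LTP is analysed per tumor.

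On the population, Table 2 in Section 2.2 admits "Child-Pugh A or B Performance status according to Eastern Cooperative Oncology Group (ECOG) ≤2". On follow-up, Section 2.5 says that "radiological examinations are required every 3 months during the first year, and once every 6 months thereafter". Overall survival is not among the primary or secondary outcomes in Sections 2.6.1 and 2.6.2.

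**The concern.** A reader takes progression-free survival to mean alive and without progression. The definition does not deliver that. Its only event is local progression, and the only condition for censoring is that local progression has not been seen. A patient who dies without it meets that condition and leaves the risk set as a censored observation. Kaplan-Meier then treats that patient as someone who could still have progressed later.

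Two things are at stake. First, LPFS is the only listed outcome with survival in its name, and overall survival is not listed, so death would lower no efficacy outcome in the article. Deaths without local progression are plausible in patients with HCC, Child-Pugh A or B liver function and performance status up to 2, followed beyond one year. Second, the result could be set beside progression-free survival figures that do count death, and that comparison would favor nsPEF.

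**Working it through.** The plan states no LPFS rate, event count or power for this outcome, so there is no figure of its own to reproduce. The check has two parts.

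**Reading the rule.** Take a patient who dies at 14 months, with no local progression on any scan.

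- Event sentence: there is no date of local progression, so no event.
- Censoring sentence: there is no evidence of local progression, so the patient is censored at last follow-up.
- No other sentence changes this.

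**Size, by illustration.** The inputs are assumptions, because the documents give no hazards:

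- hL: annual hazard of local progression
- hD: annual hazard of death without prior local progression
- both constant over time, with other censoring uninformative

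The formulas at time t are:

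- LPFS as written (death censored): exp(−hL·t)
- LPFS with death as an event: exp(−(hL + hD)·t)
- cumulative incidence of local progression with death competing: hL/(hL + hD) × [1 − exp(−(hL + hD)·t)]

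Example at 3 years with hL = 0.10 and hD = 0.05: as written, exp(−0.30) = 74.1%; with death counted, exp(−0.45) = 63.8%; excess 10.3 points.

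LPFS at 3 years:

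| hL | hD | As written | Death counted | Excess (points) |
|---|---|---|---|---|
| 0.10 | 0.02 | 74.1% | 69.8% | 4.3 |
| 0.10 | 0.05 | 74.1% | 63.8% | 10.3 |
| 0.10 | 0.10 | 74.1% | 54.9% | 19.2 |
| 0.10 | 0.20 | 74.1% | 40.7% | 33.4 |
| 0.20 | 0.02 | 54.9% | 51.7% | 3.2 |
| 0.20 | 0.05 | 54.9% | 47.2% | 7.6 |
| 0.20 | 0.10 | 54.9% | 40.7% | 14.2 |
| 0.20 | 0.20 | 54.9% | 30.1% | 24.8 |

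At 2 years the excess runs from about 3 points (hL = 0.20, hD = 0.02) to 27 points (hL = 0.10, hD = 0.20). For any hD above zero the first expression exceeds the second, so the direction does not depend on the chosen values.

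**LTP.** For the cumulative incidence of LTP, the same handling errs the other way. With hL = hD = 0.10 at 2 years, one minus Kaplan-Meier gives 1 − exp(−0.20) = 18.1%. The cumulative incidence with death competing is 0.5 × [1 − exp(−0.40)] = 16.5%. Kaplan-Meier therefore overstates LTP by about 1.6 points here, and by 0.3 points with hD = 0.02.

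**The case against.** The strongest reply is that the definition is internally clear. Read literally, the outcome is time to local progression, a legitimate quantity, and only its name is wrong. Against that quantity LPFS is not overstated at all. If anything, Kaplan-Meier makes local control look slightly worse than the cumulative incidence does. This stands in part: it makes renaming as valid a remedy as redefining. It does not save the text, because the name and the definition still disagree.

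A second reply is that the article is condensed, that censoring of deaths is inferred and not stated, and that Section 2.6 ties the outcome definitions to a cited standardization proposal that is not at hand. The inference is conceded. But the article does not leave the definition open. It states start, event and censoring, and an analysis plan that counted death would contradict it.

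Third, the size rests on assumed hazards. That is correct, and hD covers only deaths without prior local progression, so it is no higher than all-cause mortality. The low end, 3 to 4 points at 3 years, belongs in the range.

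Three stronger readings are tempting but unsupported:

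- **LPFS merely repeats LTP.** The two are close, but LTP is analysed per tumor and only after successful treatment, whereas LPFS is per patient and runs from the start of the procedure.
- **A treatment-related death would disappear from the trial.** It would not lower LPFS, but adverse events, including late ones, are a primary outcome (Section 2.6.1), and Sections 2.9 and 2.10 provide for serious-event reporting and safety monitoring.
- **Patients are censored at last contact.** The text says last follow-up, and scheduled follow-up includes imaging.

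**Conclusion.** The point holds in conditional form. Following the text as written, patients who die without local progression are censored and the result is reported as survival. If such deaths occur, the Kaplan-Meier LPFS curve lies above true survival free of local progression. A reader might infer that LPFS will be overstated whatever happens. The documents do not support that, because it is true only against the composite that the name implies and only if some patients die without local progression.

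The direction is certain under those two conditions; the size is not known. At 3 years it is about 3 to 33 points across the assumed hazards (0.10 and 0.20 per year for local progression, 0.02 to 0.20 per year for death without it). LPFS is secondary and the sample-size section attaches no hypothesis or threshold to it, so neither the primary outcome nor the calculation in Section 2.7 changes. The text should be corrected before analysis.

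**What to change.** Choose one of two routes in Section 2.6.2.

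1. **Keep the name.** Define LPFS as time from the first nsPEF procedure to local progression or death from any cause, whichever comes first. Censor patients who are alive without local progression at their last imaging assessment. Naming imaging matters because follow-up visits also include clinical and biological examinations, and only imaging can show absence of local progression.
2. **Keep the event.** Rename the outcome time to local progression and report its cumulative incidence with death as a competing event.

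Under either route, change Section 2.8 so that the cumulative incidence of LTP is estimated with death as a competing event instead of by Kaplan-Meier.

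The cost is a few sentences. Dates of death must be recorded throughout follow-up; the article does not say that they are, so the case report form should be checked. Under the first route, reported LPFS becomes less favorable. No additional patients are needed.

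### LPFS is censored at the last follow-up rather than the last negative scan: harmless while every visit carries imaging, biased upward when a scan is missed

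*Protocol article*

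**What the plan says.** Section 2.6.2 gives the event and the time origin: "LPFS is defined as the time from the commencement date of the nsPEF procedure to the date of local progression". It then gives the censoring rule: "LPFS will be censored at the date of the last follow-up, when the patient has no evidence of local progression". The last scan is not mentioned.

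Section 2.5 sets the schedule once efficacy is confirmed: "clinical, biological, and radiological examinations are required every 3 months during the first year, and once every 6 months thereafter". The same section has the images read by radiologists: "Baseline and follow-up images will be interpreted independently by all experienced diagnostic abdominal radiologists".

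Section 2.8 names the estimator: "Survival curves and cumulative incidence of LTP will be generated using the Kaplan-Meier method". It analyses LPFS per patient and LTP per tumor.

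The article states no LPFS or LTP rate, no length of follow-up, and no censoring rule for LTP. It does not say which date applies when a contact takes place without imaging.

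**The concern.** A patient seen in clinic, or contacted, without a scan shows no evidence of local progression because nobody looked. Read literally, the rule keeps that patient in the risk set up to the date of the contact. During that stretch the patient adds to the denominator and cannot contribute an event.

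The error has one direction. Moving a censoring date later leaves the detected events unchanged and can only enlarge the risk sets at later event times, so every Kaplan-Meier factor stays the same or moves closer to 1. In a single-arm trial there is no control curve carrying the same error, so the reported LPFS is simply too high.

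The date is a rule that the article states, not a detail left to another document. An analysis plan that follows the article would inherit it.

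**Working it through.** **No figure of the plan to reproduce.** The article gives no LPFS rate, event count or horizon. The check is a reading of the sections side by side, followed by an illustration on assumed inputs.

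**Step 1: when the two dates differ.** Section 2.5 joins the clinical, biological and radiological parts and makes all three mandatory at each scheduled visit. For a patient on schedule, last follow-up equals last scan and the bias is zero. The dates separate only if a scan is missed at an attended visit or if a later contact falls outside the schedule. The article plans no clinic-only or telephone follow-up.

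**Step 2: formula.** Let S(t) be the true probability of being free of local progression at time t. Let f be the share of patients who stop imaging but remain in contact to 24 months, and L the time of their last scan. With no other censoring before 24 months, the Kaplan-Meier value under last-contact censoring is one minus the share of detected events. The events missed are those after L in the unimaged group, so

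excess at 24 months = f × (mean of S(L) − S(24)).

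**Step 3: inputs.**
- From section 2.5: scans at month 1, then every 3 months in year 1 and every 6 months thereafter, taken as months 1, 3, 6, 9, 12, 18 and 24.
- Assumed: exponential local progression after month 1 at a = 10%, 20% or 30% per year, so S(t) = (1 − a)^((t − 1)/12).
- Assumed: imaging stops at a time uniform over months 1 to 24, unrelated to progression. The last scan is then at month 1, 3, 6, 9, 12 or 18 with weights 2/23, 3/23, 3/23, 3/23, 6/23 and 6/23.
- Assumed: f = 10% or 20%, and a 24-month horizon.

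**Step 4: results.** For a = 10%, mean S(L) = (2 × 1 + 3 × (0.9826 + 0.9570 + 0.9322) + 6 × (0.9079 + 0.8613)) / 23 = 0.923, and S(24) = 0.9^(23/12) = 0.817. The gap is 0.106.

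| Progression per year | True 24-month LPFS | Mean S(L) | Gap | Excess, f = 10% | Excess, f = 20% |
|---|---|---|---|---|---|
| 10% | 81.7% | 0.923 | 0.106 | 1.1 points | 2.1 points |
| 20% | 65.2% | 0.847 | 0.195 | 1.9 points | 3.9 points |
| 30% | 50.5% | 0.771 | 0.266 | 2.7 points | 5.3 points |

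Simulation under the same assumptions agrees: with f = 20%, reported LPFS is about 84%, 69% and 56%. Censoring at the last scan returns the true value to within about 0.2 point.

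**Step 5: sensitivity.**
- If contact ends 6 months after the last scan instead of running to month 24, the excess at f = 20% falls to about 1 to 2 points.
- If imaging stops earlier (at month 3, 6, 9 or 12) and progression is 15% to 35% per year, the excess is about 2 to 4 points at f = 10% and about 3 to 7 points at f = 20%. For 25% per year, counted from the procedure, mean S(L) = (0.931 + 0.866 + 0.806 + 0.750) / 4 = 0.838 and S(24) = 0.5625, so 0.20 × 0.276 = 5.5 points.
- If every contact carries a scan, f = 0 and the excess is zero.

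**The case against.** The strongest reply is that the plan already ties follow-up to imaging. Section 2.5 requires radiology at each scheduled visit, and the closing condition of the censoring sentence can be read as the last assessment negative for progression, which is the proposed fix in other words. This stands for every patient who keeps to the schedule. It does not settle the patients who leave it, and a censoring rule matters most for them. The sentence names a follow-up date, and absence of evidence is not a negative scan.

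The size is also open to objection. With about 160 patients and LPFS near 65%, the binomial 95% half-width is 1.96 × √(0.65 × 0.35 / 160) ≈ 7 points, which is more than the excess in the main scenarios. That stands as a reason for low severity. It does not remove the bias, which is systematic.

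Three stronger readings are tempting, and the documents do not support them:
- A reader might take "Assuming a 20% rate of withdrawal or loss during follow-up" (section 2.7) as the share of patients seen without scans. It is not. Patients who withdraw or are lost leave follow-up, so their last follow-up date stops advancing too. The figure serves the sample size for complete ablation. The 20% case above is an assumed upper-end scenario.
- A reader might infer that the Cox results are shifted in favour of the device. Section 2.8 uses Cox only to look for prognostic factors within one arm. The model has no device term, and excess time at risk spread evenly over subgroups favours nobody systematically.
- A reader might infer that LTP is censored wrongly as well. The article states no censoring rule for LTP, so the same problem arises there only if the LPFS date is carried over.

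**Conclusion.** The point holds in a limited form. The stated date does not match the way the event is found, and the mismatch can act only for patients who miss a scan or have an unscheduled contact without imaging. For them it credits unverified time and pushes Kaplan-Meier LPFS upward.

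The documents do not give the size. The range of about 1 to 3 points (10% seen but not imaged) to 2 to 5 points (20%) at 24 months rests on assumed progression of 10% to 30% per year, contact kept up to month 24, and imaging that stops independently of progression. The article does not show that any patients will be followed without scans, so this is a risk in the wording and not a demonstrated bias.

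Severity is low. LPFS is a secondary endpoint without a stated hypothesis or threshold, and the complete ablation rate and the sample size are untouched.

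**What to change.** Replace the censoring sentence in section 2.6.2 with: *Patients without local progression are censored at the date of their last imaging assessment showing no local progression (at the procedure date if there is none).* Use the same date for LTP, applied per tumor.

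The wording says imaging assessment without naming a modality, because after month 1 section 2.5 asks only for radiological examinations.

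The cost is one sentence. The scans are already required, so nothing new has to be collected. Recorded follow-up becomes slightly shorter and intervals slightly wider. If every follow-up does carry a scan, no result changes. The change does not repair imaging that stops for reasons linked to progression, since last-scan censoring also assumes that the two are unrelated.

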### 2.7 Calculation of Sample Size

Because this is a pilot study, there is currently no data on the complete ablation rate of nsPEF for the treatment of HCC. Previous studies showed a 77.3%-86% rate of complete ablation after the first IRE (with a traditional microsecond duration) in patients with HCC that was not appropriate for thermal ablation (11, 33). Our hypothesis is that 80% of tumors treated by nsPEF will achieve complete ablation by the 1-month follow-up. For the single arm OPC hypothesis, employing 80% power and with a 2.5% one-sided α, then 160 patients will be required. Assuming a 20% rate of withdrawal or loss during follow-up, 192 participants should be enrolled.

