**Methods and analysis:**

We will conduct an open-labeled, single-arm, prospective, multicenter, and objective performance criteria trial. One hundred and ninety-two patients with HCC, in which the tumor is located immediately (<0.5 cm) adjacent to the portal vein, hepatic veins, bile duct, gastrointestinal tract, or diaphragm, will be enrolled among 4 academic medical centers. The primary outcomes are the rate of complete ablation at 1 month and adverse events. Secondary outcomes include technical success, technique efficacy, nsPEF procedural characteristics, local tumor progression, and local progression-free survival.

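### The 20% loss allowance in section 2.7 is computed as 160 × 1.20 = 192 instead of 160/0.80 = 200, so 192 enrolled leaves 153 to 154 evaluable at that loss rate: wrong as written, minor

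*Protocol article*

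**What the plan says.** Section 2.7 (Calculation of Sample Size) sets the trial up as a single-arm comparison with an objective performance criterion (OPC). The expected rate is stated as: "Our hypothesis is that 80% of tumors treated by nsPEF will achieve complete ablation by the 1-month follow-up". The size follows: "employing 80% power and with a 2.5% one-sided α, then 160 patients will be required". The next sentence adds the allowance for attrition: "Assuming a 20% rate of withdrawal or loss during follow-up, 192 participants should be enrolled".

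The abstract (Methods and analysis) carries the same enrolment target: "One hundred and ninety-two patients with HCC". Neither place defines the 20% as a share of the evaluable number, and no other loss rate is given. The OPC threshold that the 80% is tested against is not printed as a number.

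**The concern.** Only enrolled patients can withdraw or be lost, so a loss rate is a fraction of enrolment. The enrolment that leaves a required number is that number divided by one minus the loss rate. The printed 192 is instead the required number multiplied by one plus the loss rate, a common slip that always gives too few.

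At stake is whether the sample size paragraph for a primary outcome is consistent with itself. There is also a practical side. Section 2.10 asks the DSMB to watch the sample size assumptions and the losses to follow-up. A board that takes 20% as the planned-for loss would see nothing amiss while the evaluable number fell below 160, because the loss that 192 can absorb is lower than 20%.

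**Working it through.** **Inputs, all from section 2.7:** required number 160; loss rate 20%; enrolment 192; one-sided α 2.5%; power 80%; expected complete ablation rate 80%. Not printed: the OPC threshold p0.

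**1. Reproduce the plan's figure.** 160 × (1 + 0.20) = 192. The match is exact, so rounding is not the explanation.

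**2. Enrolment that leaves 160 after 20% loss.** 160/(1 − 0.20) = 160/0.80 = 200, which is 8 more than printed.

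**3. What 192 leaves at 20% loss.** 192 × (1 − 0.20) = 153.6, so 153 to 154 evaluable, 6 to 7 below 160 (6.4/160 = 4%).

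**4. Loss that 192 can absorb.** (192 − 160)/192 = 32/192 = 16.7%.

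Steps 1 to 4 need no assumption beyond the printed figures. The power effect does need one, because p0 is missing.

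**5. Power, conditional on p0.** With p1 = 0.80, the usual normal approximation for one proportion (null variance in the critical value, alternative variance in the power) is

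power = Φ{ [(p1 − p0)√n − 1.96 √(p0(1 − p0))] / √(p1(1 − p1)) }.

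*(a) p0 chosen so that the plan's statement is true, i.e. 160 gives 80% power.* This solves to p0 ≈ 0.7026.
- n = 160: [0.0974 × 12.649 − 1.96 × 0.4571]/0.40 = 0.840, power 80.0%.
- n = 153: [0.0974 × 12.369 − 1.96 × 0.4571]/0.40 = 0.772, power 78.0%.
- n = 154: power 78.3%.

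*(b) p0 assumed to be a round 0.70.*
- Required n for 80% power: [1.96 × 0.4583 + 0.8416 × 0.40]² / 0.10² = 152.5, i.e. 153.
- n = 160: power 82.0%. n = 153: power 80.1%.

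In both cases going from 160 to 153 costs about 2 points. Whether the result falls below 80% depends on a threshold that the document does not state.

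**The case against.** The arithmetic is hard to dispute; the argument is about how much it matters, and most of that argument stands.

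- **The gap is small.** It is 8 enrolled patients, or 6 to 7 evaluable. The endpoint and the test do not change.
- **The efficacy endpoint is early.** Complete ablation is read on the 1-month MRI, while section 2.5 continues follow-up every 3 months in the first year and every 6 months after that. If the 20% spans the whole follow-up, fewer will be missing at 1 month, and any loss up to 16.7% leaves 160. Patients taken out of the trial after a failed second session already have their 1-month result. This limits the practical effect. It does not make the paragraph right, since 20% is the only rate the document gives and it is the one used in this calculation.
- **A reader might infer that the trial misses its stated 80% power.** The document does not support that as a flat statement. The 78% figure rests on a threshold solved backwards from 160; at an assumed threshold of 70%, the normal approximation still reaches 80% at 153.
- **A reader might also infer a larger loss by trying higher thresholds.** At 71.1%, for example, the formula gives about 70% power at 153. But at that threshold it gives only about 72% at 160 and asks for about 190 patients, which contradicts the plan's own claim for 160. The drop due to the inflation slip is again about 2 points.
- **An exact binomial test does not settle it.** Against 70%, exact power is 81.4% at 160, 78.7% at 153 and 77.5% at 154, but also 78.3% at 158 and 81.8% at 155. The difference between 160 and 153 lies within the saw-tooth of a discrete test.

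**Conclusion.** Wrong as written, and minor. The figures 160, 20% and 192 cannot all be true: 192 corresponds to a 16.7% loss, and a 20% loss leaves 153 to 154 evaluable. That conclusion rests only on the printed numbers and on the ordinary meaning of a loss rate as a share of those enrolled.

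The consequence for power is about 2 points and is conditional. It assumes a true rate of 80%, the normal approximation above, and that 20% of patients really lack a 1-month result. If 160 gives exactly 80% power, 153 to 154 gives about 78%; if the threshold is 70%, power at 153 is still about 80%. The 160 is taken here as given, since it cannot be reproduced without the threshold. The document does not support saying that the trial is materially underpowered.

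**What to change.** Correct section 2.7 in one of three ways:

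1. Keep 192 and 160, and state that 192 allows for a loss of 16.7% and leaves 160 evaluable.
2. Keep 192 and 20%, state that about 153 patients will be evaluable, and give the power recomputed at the actual OPC threshold. The 78% above should not be copied in, because it rests on an inferred threshold.
3. Keep 160 and 20%, and change enrolment to 200.

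Options 1 and 2 are changes of wording only and leave the abstract's 192 as it is. Option 3 costs 8 more patients and a matching change in the abstract. Since the efficacy endpoint is read at 1 month, option 1 is the simplest if the sponsor is content that loss by then will not exceed 16.7%.
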